## Abstract

**Background:**

Stress-related disorders such as anxiety and depression are highly prevalent and cause a tremendous burden for affected individuals and society. In order to improve prevention strategies, knowledge regarding resilience mechanisms and ways to boost them is highly needed. In the Dynamic Modelling of Resilience – interventional multicenter study (DynaM-INT), we will conduct a large-scale feasibility and preliminary efficacy test for two mobile- and wearable-based just-in-time adaptive interventions (JITAIs), designed to target putative resilience mechanisms. Deep participant phenotyping at baseline serves to identify individual predictors for intervention success in terms of target engagement and stress resilience.

**Methods:**

DynaM-INT aims to recruit *N* = 250 healthy but vulnerable young adults in the transition phase between adolescence and adulthood (18–27 years) across five research sites (Berlin, Mainz, Nijmegen, Tel Aviv, and Warsaw). Participants are included if they report at least three negative burdensome past life events and show increased levels of internalizing symptoms while not being affected by any major mental disorder. Participants are characterized in a multimodal baseline phase, which includes neuropsychological tests, neuroimaging, bio-samples, sociodemographic and psychological questionnaires, a video-recorded interview, as well as ecological momentary assessments (EMA) and ecological physiological assessments (EPA).

Subsequently, participants are randomly assigned to one of two ecological momentary interventions (EMIs), targeting either positive cognitive reappraisal or reward sensitivity. During the following intervention phase, participants' stress responses are tracked using EMA and EPA, and JITAIs are triggered if an individually calibrated stress threshold is crossed. In a three-month-long follow-up phase, parts of the baseline characterization phase are repeated. Throughout the entire study, stressor exposure and mental health are regularly monitored to calculate stressor reactivity as a proxy for outcome resilience. The online monitoring questionnaires and the repetition of the baseline questionnaires also serve to assess target engagement.

**Discussion:**

The DynaM-INT study intends to advance the field of resilience research by feasibility-testing two new mechanistically targeted JITAIs that aim at increasing individual stress resilience and identifying predictors for successful intervention response. Determining these predictors is an important step toward future randomized controlled trials to establish the efficacy of these interventions.

**Supplementary Information:**

The online version contains supplementary material available at 10.1186/s40359-023-01249-5.

## Introduction

### Background

Stress-related mental disorders such as depression and anxiety disorders reside among the leading causes for disability worldwide [1–3] and cause a considerable burden to affected individuals, society, and the economy [4]. The general prevalence of mental disorders is particularly high in late teens and young adults in their twenties [5], with depression and anxiety showing a high rate of recurrence or persistence [6]. Although the link between stress and mental disorders has been well known for quite some time, the prevalence of stress-related disorders has not decreased during the last years [7]. Next to a failure to correctly implement clinical practice guidelines, one likely cause is the lack of appropriate and accessible prevention programs [7]. To inform prevention programs and help identifying possible prevention targets, research should ideally not only investigate contributing factors and mechanisms related to vulnerability, dysfunction, and psychopathology, but also investigate resilience, in order to identify factors and mechanisms that help people to stay healthy despite experiencing adversity [8].

Resilience can be defined as sustained or quickly recovering good mental health during and after experiencing adversity [9, 10]. This definition of resilience as an outcome rather than a trait reflects the difficulty to individually predict good long-term mental health responses to stressor exposure from a person’s stable features or predispositions and acknowledges that staying mentally healthy appears to result from putatively dynamic and complex processes allowing successful adaptation to stressors [8, 10–14]. These processes are not only determined by individual predisposing factors (so-called ‘resilience factors’, e.g., a certain genotype, stable personality traits, or beliefs) but also by characteristics specific to the adverse events or circumstances and an interplay between the two, and they involve the activation of protective mechanisms (‘resilience mechanisms’) at the level of the individual or the environment. Defining resilience as an outcome implies that resilience research should make use of longitudinal study designs, assessing adversity as well as mental health at several time points to capture the dynamic nature of occurring stressors and the possible subsequent changes in mental health [8, 10]. Another necessary element of resilience studies are assessments of resilience factors or mechanisms that can be linked to the outcome and which should ideally also be examined repeatedly, to thus uncover processes of adaptation [8].

Although some resilience factors are quite stable and will (mostly) not change much over the course of life (e.g., one’s genotype), other resilience factors are malleable and can undergo change, for example, triggered by the experience of adversity itself (e.g., one’s individual repertoire of emotion regulation strategies, which might increase after learning a new strategy during a period of adversity). Such individual adaptations have been termed allostatic resilience processes, as opposed to homeostatic resilience processes in which protective mechanisms are successfully engaged but an individual’s mode of operation in coping with adversity is not lastingly altered [12]. Malleable resilience factors are thus natural targets for prevention programs that aim to increase individual resilience [10, 15]. Studies have investigated several interventions designed to increase resilience, many of which focus on cognitive-behavioral or mindfulness-based methods, or a mix of both [16]. However, so far, many intervention studies to foster resilience present substantial methodological deficiencies such as missing a clear definition and operationalization of resilience, investigating effects of the intervention on single resilience factors instead of on outcome resilience, or the lack of baseline diagnostics or long-term follow-ups [17].

### The current study

The interventional study DynaM-INT of the EU Horizon 2020 project consortium DynaMORE (‘Dynamic Modelling of Resilience’ [18]) is designed to investigate two mobile- and wearable-based just-in-time adaptive interventions (JITAIs) aimed at fostering resilience and to predict their success based on participants’ baseline characteristics. The target sample consists of students and apprentices between 18 and 27 years. During this period of life, several mental disorders appear for the first time or even have their peak prevalence [19], and students seem to be a particularly vulnerable group for stress-related psychopathology [20–24]. Youth and emerging adults are also among the groups that were most strongly mentally affected by the COVID-19 pandemic [25]. Insofar as early-onset stress-related problems are often associated with life-long mental vulnerability, investment in the mental health of emerging adults is likely to yield lasting gains and to be economically particularly efficient [26]. To ensure that we specifically include at-risk individuals, inclusion criteria include the prior experience of at least three negative life events that are perceived as burdensome [27], and a score in the mid-to-high range of the 28-item version of the General Health Questionnaire (GHQ) [28], a self-report instrument that captures internalizing symptomatology.

As a prospective-longitudinal resilience study, DynaM-INT entails a multimodal baseline characterization phase that focuses on potential resilience factors followed by longitudinal, biweekly assessments of a small number of hypothesized key resilience factors, considered potentially malleable, as well as of experienced stressors (E) and mental health problems (P) throughout the course of the study (online monitoring questionnaires). See Fig. 1 for a schematic overview of the study timeline.

**Fig. 1 Fig1:**
[figure not shown]
Study timeline. The study involves a baseline characterization phase, an ecological momentary intervention phase, and a follow-up phase. On-site assessments are done at the beginning of the baseline and follow-up phases. In Berlin, Tel Aviv, and Warsaw, all baseline on-site assessments are conducted on one day, while in Mainz and Nijmegen, these baseline assessments are split into two days: M.I.N.I. interview and blood sampling are done on day 1, all remaining procedures are performed on day 2. On both testing days in Mainz and Nijmegen, a urine drug test is conducted. On-site assessments are complemented by regular online monitoring of stressors, mental health problems, and selected resilience factors. Abbreviations: EMA, ecological momentary assessment; EMI, ecological momentary intervention; EPA, ecological physiological assessment; JITAI EMI, just-in-time ecological momentary intervention; M.I.N.I., Mini-International Neuropsychiatric Interview

Repeated E and P monitoring implements the Frequent Stressor and Mental Health Monitoring (FRESHMO) paradigm, which we have developed specifically for the purpose of longitudinal resilience studies [12]. E and P scores are used to calculate stressor reactivity (SR) scores, the primary outcome variable and a proxy for outcome resilience [12] using a residualization approach [29, 30]. Specifically, we regress individuals’ mental health problems P on their stressor exposure E, both across all monitoring time points, to determine our sample’s normative E-P relationship. For any given individual timepoint, a participant’s regression residual from this normative E-P relationship reflects their SR relative to their current stressor exposure and the sample’s normative reactivity. Thus, positive residuals indicate that the participant experiences more mental health problems P than would be expected given their stressor exposure E (higher SR) at this time point, whereas negative residuals mean that a participant has fewer mental health problems than would be predicted at their given stressor exposure (lower SR) at this time point. Within-participant SR score time-courses will be calculated to investigate temporal fluctuations in reactivity and set these into relation with the interventions (see below) and with potential changes in resilience factors resulting from the interventions [12]. The repeated assessment of several potential resilience factors in the online monitoring questionnaires is complemented by repetitions of parts of the baseline characterization phase after six and eight months (‘follow-up phase’; Fig. 1).

Importantly, upon completion of the baseline characterization phase, participants enter an ecological momentary intervention (EMI) phase where they are randomly assigned to one of two EMIs designed by our consortium that aim to improve two distinct resilience factors: ‘ReApp’, targeting positive cognitive reappraisal of recent stressful or negative events [64], or ‘Imager’, targeting reward sensitivity by positive mental imagery [31, 65]. The interventions are accompanied by ecological momentary assessments (EMA) using smartphones and ecological physiological assessments (EPA) using wearables (wristbands) to assess mood and stress reaction patterns in real time during real life and to allow triggering of EMIs as JITAIs at times of high stress.

Specifically, after calibration of individual EMA and EPA thresholds for stress responses on study devices as part of baseline characterization (‘calibration week’, see Fig. 1), participants are first trained in using the assigned intervention on their own phones without concurrent EPA (‘training weeks’). Then, participants are administered three EMI ‘booster weeks’ on study devices during which real-time EMA and EPA data is used to trigger interventions specifically at moments when participants’ stress levels cross the individual threshold established during the calibration week (that is, JITAI). The rationale behind this approach is that these interventions are thought to be most effective when participants apply the previously learned cognitive strategies at moments when they are needed most [32]. These booster weeks happen every four weeks over the period of three months in the EMI phase. Between the booster weeks, participants are encouraged to continue practicing the assigned intervention (‘practice weeks’) on their own phones. Supplementary Figure S1 depicts the different assessments per week type [see Additional file 1].

### Research questions

The study is primarily designed to identify baseline predictors of the effect of our JITAIs on stressor reactivity as well as target engagement, in order to inform the design of future randomized controlled trials testing the efficacy of these interventions. To prepare predictor identification, we will first evaluate intervention feasibility and efficacy. We will evaluate feasibility by testing whether EMIs with a JITAI element that uses mobile phones and wristbands to trigger interventions specifically at times of high stress can be conducted on a large scale, focusing on i) technical implementation (feasibility research question 1, fQ1) as well as ii) participant adherence (fQ2) and iii) participant experience (fQ3).

To preliminarily evaluate the efficacy, we will quantify whether, relative to baseline, the interventions are accompanied by, i) reductions in SR scores (efficacy research question 1, eQ1) and ii) increases in respective target engagement (eQ2). For target engagement specifically, we will assess changes in the use frequency of positive cognitive reappraisal during and after the ReApp JITAI and changes in reward sensitivity during and after the Imager JITAI. These patterns could be interpreted as further evidence for intervention success [31, 64]. The efficacy tests primarily use the biweekly assessed self-report measures of stressor exposure, mental health, positive cognitive reappraisal, and reward sensitivity.

Our efficacy tests will be further facilitated by the possibility to compare DynaM-INT results to data from the purely observational DynaM-OBS study [33], to which DynaM-INT is the follow-up study. DynaM-OBS uses the same type of baseline characterization and repeated assessment of E, P, and resilience factors (specifically positive cognitive reappraisal) in a study sample and over a time period comparable to DynaM-INT. DynaM-OBS thus provides us with an estimate of the natural course of SR and target engagement measures that can be used as a discovery sample and as a background against which the effects of the interventions in DynaM-INT can be assessed. Note that DynaM-OBS cannot be considered a formal control condition, but may provide an informal effect estimate justifying future randomized controlled trials (RCTs) with appropriate control conditions.

Following these evaluations of feasibility (fQ1-3) and efficacy (eQ1-2), we will address our primary research questions, namely, examining variables assessed in the baseline characterization phase to identify those that moderate (predict) the efficacy of either of the two interventions on i) stressor reactivity (primary research question 1, pQ1) and ii) target engagement (pQ2). The exact list of potential moderator variables to be examined, besides initial levels of positive cognitive reappraisal and reward sensitivity, will depend on the results of the DynaM-OBS study. Specifically, in DynaM-INT we will focus on predictors of low SR scores obtained from DynaM-OBS. These investigations aim to prepare future RCTs intended to test the efficacy of these interventions where baseline data serves to guide intervention administration only to individuals that are likely to benefit from a given intervention.

As a follow-up to our two primary research questions, we will examine whether the anticipated reductions in stressor reactivity are preceded or accompanied by the anticipated increases in target engagement (secondary research question, sQ1), which would suggest that the interventions execute their effects via the targeted resilience mechanisms.

A tertiary set of main research questions (tertiary research question, tQ) to be answered with DynaM-INT is related to Positive Appraisal Style Theory of Resilience (PASTOR) [10], the core theoretical framework of the DynaM-INT study. Positive appraisal style (PAS) is the tendency of an individual to appraise potential stressors in a positive (i.e., non-negative) way while at the same time avoiding delusionally positive appraisals. Positive appraisers typically generate appraisals that range from realistic to slightly unrealistically positive. Such a positive appraisal style is thought to enable the individual to exhibit optimal, fine-tuned stress reactions that are sufficient to cope with the stressor but that do not exceedingly exhaust resources, which reduces the likelihood of developing mental health problems in adverse life situations. PASTOR claims that PAS is the key proximal resilience factor in that the effects of all other resilience factors on outcome resilience are mediated by their effects on PAS [10]. In PASTOR, positive cognitive reappraisal is one important sub-class of cognitive processes that generate positive appraisals [10, 34], and it is therefore claimed that individuals who use positive cognitive reappraisal more frequently and/or more efficiently are likely to have higher PAS. Thus, positive cognitive reappraisal is an important component of PAS, which is why it is here targeted by the ReApp EMI. By contrast, reward sensitivity, as targeted by the Imager EMI, is a separate potential resilience factor that is thought to promote resilience insofar as it helps individuals generally appraising stressful situations in a more benign fashion, by better integrating positive information into the overall appraisal. Hence, eventually, one can assume that both the ReApp and the Imager EMIs promote resilience by promoting PAS.

PAS (like positive cognitive reappraisal and reward sensitivity) is considered a malleable resilience factor. Accordingly, in our study design, self-report measures of PAS (like measures of the two EMI targets) are not only taken in the questionnaire battery of the baseline characterization phase but also when the characterization is repeated at follow-up as well as in the biweekly online monitoring questionnaires (see Fig. 1). This allows us to ask whether the interventions are accompanied by increases in PAS relative to baseline (tQ1), whether the anticipated reductions in stressor reactivity are preceded or accompanied by the anticipated increases in PAS (tQ2), and whether the anticipated increases in PAS are preceded or accompanied by the anticipated increases in target engagement (tQ3). These findings would suggest that the interventions promote resilience by promoting PAS. Beyond intervention effects, we will examine whether individuals with high baseline PAS show less stressor reactivity (tQ4) and whether changes in PAS throughout the course of the study will be accompanied by inverse changes in stressor reactivity (tQ5), irrespective of the treatment.

The research questions are summarized in Table 1; additional exploratory research questions are outlined in the analysis section. The DynaM-INT data set will be made available to researchers to address other possible research questions.

**Table 1 Tab1:** List of research questions

Type	Nr	Research Question
Feasibility	fQ1	Is JITAI using mobile phones and wristbands to trigger interventions specifically at times of high stress technically feasible?
	fQ2	Do participants adhere to the JITAI?
	fQ3	How do participants experience the JITAI?
Efficacy	eQ1	Are the interventions accompanied by reductions in stressor reactivity relative to baseline?
	eQ2	Are the interventions accompanied by increases in target engagement relative to baseline?
Primary	pQ1	Can we identify predictors in the baseline characterization data for the effects of each of the two interventions on stressor reactivity?
	pQ2	Can we identify predictors in the baseline characterization data for the effects of each of the two interventions on target engagement?
Secondary	sQ1	Are the anticipated reductions in stressor reactivity preceded or accompanied by the anticipated increases in target engagement?
Tertiary	tQ1	Are interventions accompanied by increases in PAS relative to baseline?
	tQ2	Are the anticipated reductions in stressor reactivity preceded or accompanied by the anticipated increases in PAS?
	tQ3	Are the anticipated increases in PAS preceded or accompanied by the anticipated increases in target engagement?
	tQ4	Do individuals with high baseline PAS show less stressor reactivity?
	tQ5	Are changes in PAS throughout the course of the study accompanied by inverse changes in stressor reactivity?

In the DynaM-INT study, we attempt to answer multiple research questions, divided in feasibility and efficacy questions, as well as primary, secondary and tertiary main research questions

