### Participants

In total, *N* = 250 healthy male and female participants are planned to be recruited at the five study sites (*N* = 50 each). Where a study site cannot fulfil the recruitment goal, other sites will attempt to compensate. Participants need to be 18–27 years, studying or in vocational training, have experienced at least three stressful life events [27] that they perceived as burdensome before inclusion, and report elevated levels of internalizing symptoms (a score of ≥ 20 in the GHQ, 28-item version [28]). All inclusion criteria are provided in Table 2.

**Table 2 Tab2:** List of inclusion criteria and format in which they were assessed

Nr	Criterion	Format
1	Age between 18 and 27	Online
2	3 or more life events rated as burdening [27]	Online
3	GHQ-28 score of 20 or higher [28]	Online
4	Body mass index between 18 and 27	Online
5	Currently studying or in vocational training	Online
6	Proficiency in the official language of the country of study enrollment (minimum level of C1 in the Common European Framework of Reference for Languages)	Online
7	Eligibility to participate in ecological physiological assessment using a wearable device (no skin disease in the wrist or chest area and no medical condition that increases risk of infection through electrodes, no medication with phototoxic side effects)	Online
8	The participant has a smartphone with iOS or Android operating system	Online
9	No lifetime diagnosis of any severe mental or organic disorder that affects neurodevelopment due to its pathological mechanism or treatment (e.g., schizophrenia, bipolar disorder, anorexia/bulimia nervosa, attention deficit hyperactivity disorder, autism spectrum disorder, meningitis, epilepsy, multiple sclerosis, stroke, brain cancer, brain concussion, or coma)	Online + interview
10	Eligibility for undergoing the functional magnetic resonance imaging protocol (normal or corrected-to-normal eyesight, no hearing impairment, no claustrophobia, no non-removable ferromagnetic metal in or at the body, not pregnant, no large tattoo in head or neck area)	Online + interview
11	No diagnosis within 9 months before inclusion of any mental disorder other than a mild depressive episode (ICD F32.1), tobacco abuse/dependence (ICD F12), or substance abuse, as assessed using the Mini-International Neuropsychiatric Interview (M.I.N.I.)[36]	Interview
12	The participant has not participated in the previous DynaM-OBS study or any study using an EMI similar to ReApp or Imager	Interview

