**Questionnaires used to assess secondary resilience and risk factors**		
	Anxiety Sensitivity Index (ASI)	Beliefs of negative implications of anxiety experiences, 18 items [81]
	Dimensional Anhedonia Rating Scale (DARS)	Multiple facets of hedonic function such as desire, motivation, effort, and consummatory pleasure across hedonic domains, 17 items [82]
	Maltreatment and Abuse Chronology of Exposure (MACE)	Abuse and neglect during development, 52 items [83]
	Perceived Social Status Scale (PSS-S)	Subjective socioeconomic status by means of a drawing of a ladder with 10 rungs, described to represent where people stand in society. Participants are instructed to indicate the rung that best represents where they stand on the ladder. Additionally, the same question is asked for the dimensions of academic and occupational status [84]
	Ruminative Thought Style Questionnaire (RTS)	Components of ruminative thinking including problem-focused thoughts, counterfactual thinking, repetitive thoughts, and anticipatory thoughts, 15 items [85]
	Sensitivity to Punishment and Sensitivity to Reward Questionnaire (SPSRQ)	Tendency for aversive and appetitive behavior, 48 items [86]
	State Trait Anxiety Inventory (STAI)	Symptoms of anxiety as a state and as a general trait, respectively, 40 items [87]
	Toronto Alexithymia Scale (TAS-20)	Deficiency in understanding, processing, or describing emotions, 20 items [88]

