##### Calibration week

In the week following the on-site baseline assessment day(s), EMA and EPA data is collected. Participants use a study smartphone (Motorola Moto E6 Play in Berlin, Mainz, Nijmegen, and Warsaw; Xiaomi Redmi 7/7A in Tel Aviv) with the RADAR aRMT app (adapted for the use in DynaM-INT) for EMA data collection [51] and the Chill + wristband (developed by IMEC [52]) for EPA data collection. Participants receive a thorough explanation about the EMA and EPA devices, applications, and procedures.

Each day during usual waking hours (between 7:30 and 22:30), questionnaires of around 2 min length each are sent at 10 different time points (“beeps”) via push notifications to the smartphone. Each notification is semi-randomly scheduled to be sent out in a block of 90 min. The beep schedule is the same for all participants and is specified in Supplementary Table S1; EMA content can be found in Supplementary Figure S2 [see Additional file 1]. Each beep questionnaire remains online for 10 min, and participants receive a reminder notification 5 min after the initial beep notification.

EPA data is collected via the wristband for 16 h per day. The wristband also features a “stress” button that participants are instructed to press when they experience a stressful event. The calibration week lasts for six days.

All EMA data collected with the RADAR aRMT app is immediately and automatically uploaded to a server at the Donders Institute, where the initial feature extraction takes place in real time. After completion of each EMA questionnaire (via the RADAR aRMT app) participants are redirected to the DynaMORE Chill + app (developed by IMEC for the use in DynaM-INT) to upload 10 min of EPA data acquired right before each EMA notification to the server at the Donders Institute, where relevant features are extracted and motion-related artifacts are removed. A complete list of features is given in Supplementary Table S2 [see Additional file 1].

After the calibration week has finished, participants come back to the lab to return study devices. All data collected with the Chill + app is downloaded by the researchers for additional offline feature extraction (of the entire 6 days × 16 h EPA data). The baseline characterization phase is completed by randomly assigning one of the interventions to the participant based on a predetermined randomization sheet (computerized random numbers to 1 of 2 EMIs).

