#### Online questionnaires

The assessment schedule of online questionnaires is outlined in Table 3.

Items of the extended questionnaire battery assess socio-demographic information at month 1 (study baseline), and general health, stressor exposure, mental health, as well as potential psycho-social resilience and risk factors (collectively termed ‘RFs’) at months 1, 6 and 8. RFs included in the battery are assessed as relatively stable styles or traits (i.e., the typical way or tendency in which a person reacts to life experiences). The measures included in the extended questionnaire battery at study baseline will be employed as potential moderators of intervention effects on the primary outcome variables, SR scores and target engagement (see primary research questions in Introduction and Table 1).

The biweekly monitoring questionnaires administered throughout the course of the study assess further information on stressor exposure, mental health, and central RFs necessary to calculate SR scores and target engagement measures as the main outcome variables. To build biweekly SR scores, these questionnaires contain repeated measures of mental health problems (P), assessed by the GHQ-28 [28], and on stressor exposure (E), assessed primarily via a daily hassles list (MIMIS, [44]). Further E measures assessed during the biweekly monitoring, related for example to the COVID pandemic, will be explored for their additional relevance when calculating SR scores (see Table 3).

Target engagement for ReApp is operationalized as the self-reported use frequency of positive cognitive reappraisal (assessed with the items on acceptance, positive reappraisal, putting into perspective, and distancing in the PASS-process questionnaire) and for Imager as the self-reported reward sensitivity (assessed using anticipatory items of the TEPS questionnaire). While RFs included in the extended questionnaire battery are assessed as relatively stable styles, RFs included in the biweekly monitoring were altered to be assessed as modes (i.e., the extent to which the RF was used or experienced in the past two weeks [42]). Complementary and secondary to the biweekly mode assessments, target engagement will also be determined from the corresponding style measures in the extended questionnaire battery.

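### The wording of the pQ1 moderator pool does not exclude the baseline GHQ-28, although that score is part of baseline stressor reactivity

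*Protocol article*

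**What the plan says.** All references are to the protocol article.

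- **Aim.** Research questions describes the primary task as "examining variables assessed in the baseline characterization phase to identify those that moderate (predict) the efficacy of either of the two interventions".
- **Moderator pool, broad wording.** Online questionnaires (under Materials) lists mental health among the contents of the extended battery, next to resilience and risk factors (RFs). It then states: "The measures included in the extended questionnaire battery at study baseline will be employed as potential moderators of intervention effects on the primary outcome variables". One of the outcomes named there is SR.
- **Moderator pool, narrower wording.** Primary research questions (pQ) refers to baseline variables with RFs in brackets. Table 5 lists the GHQ-28, PSS-10 and SCL-90-R under mental health, apart from the RFs. Research questions makes the list, beyond reappraisal and reward sensitivity, depend on the observational study: "we will focus on predictors of low SR scores obtained from DynaM-OBS".
- **Outcome.** The current study defines SR as the residual of mental health problems (P) regressed on stressor exposure (E) over all monitoring time points. P is the GHQ-28: the monitoring questionnaires contain "repeated measures of mental health problems (P), assessed by the GHQ-28".
- **Schedule.** Table 3 shows one GHQ-28 at month 1, week 1. It also marks the PSS-10, the SCL-90-R and the secondary RFs in that week. The secondary RFs include the STAI, described in Table 5 as "Symptoms of anxiety as a state and as a general trait".
- **Test.** Preparatory efficacy questions (eQ) compares intervention-phase with baseline measurements. Primary research questions (pQ) tests the interaction of a baseline variable with that effect, first within each intervention group. Allocation is by "computerized random numbers to 1 of 2 EMIs", so no arm is untreated.

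**The concern.** The month 1, week 1 GHQ-28 has two roles. It is a baseline battery measure, and it is the P term of one of the three baseline SR scores. Whatever is accidental in it (measurement error, a bad fortnight) raises the moderator. It also raises the baseline SR mean, so the change from baseline looks more favourable. Within a single arm this coupling looks the same as people with more symptoms benefiting more, and it appears even when the intervention does nothing.

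pQ1 is a primary question, and its stated purpose is to let later trials offer an intervention only to those likely to gain. An artefact in the list of predictors would pass directly into the eligibility rules of those trials.

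**Working it through.** The plan states no alpha, power, within-person correlation or error rate, so there is no figure to reproduce. The check asks how often the interaction test rejects when neither intervention has any effect.

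**Inputs from the document**
- Sample: "250 healthy male and female participants are planned to be recruited at the five study sites". Two interventions, equal split assumed: 250 / 2 = 125 per arm.
- Baseline monitoring waves: 3 (Table 3: M1 w1, M1 w3, M2 w1).
- Intervention-phase waves: 7 (Table 3: M2 w4, then w2 and w4 of M3, M4 and M5).

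**Assumptions**
- Two-sided alpha 0.05.
- Stable share of SR variance (ICC) 0.3 to 0.8.
- Stressor exposure explains 25% of GHQ-28 variance.

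**Step 1: closed form, independent errors, no entry selection.** Scale SR variance to 1. Let D be the mean SR of the 7 intervention waves minus the mean SR of the 3 baseline waves.
- Cov(GHQ at M1 w1, D) = −(1 − ICC)/3
- Var(D) = (1 − ICC)(1/3 + 1/7) = 0.476(1 − ICC)
- Var(GHQ) = 1/(1 − 0.25)
- r = −[(1 − ICC)/3] / √[0.476(1 − ICC)] × √0.75 = −0.418 √(1 − ICC)
- Rejection rate ≈ Φ(atanh|r| × √(n − 3) − 1.96), with √122 = 11.05

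| ICC | r | atanh of abs(r) × 11.05 | Rejection |
|---|---|---|---|
| 0.3 | −0.350 | 4.04 | 98% |
| 0.5 | −0.296 | 3.37 | 92% |
| 0.6 | −0.265 | 2.99 | 85% |
| 0.7 | −0.229 | 2.58 | 73% |
| 0.8 | −0.187 | 2.09 | 55% |

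**Step 2: simulation, n = 125.**
- A fitted random-intercept model (SR on phase × GHQ, 150 runs per ICC) gave 93%, 81%, 74% and 55% at ICC 0.5, 0.6, 0.7 and 0.8.
- Entry requires a GHQ-28 of 20 or more. With that represented by a screening score above the population median (800 runs per cell), the rates were 99%, 97%, 96%, 92% and 85% for ICC 0.3, 0.5, 0.6, 0.7 and 0.8.
- Adding AR(1) errors of 0.6 to that selection gave 100%, 99%, 96%, 91% and 81%.
- Nearly all rejections run in the direction of higher GHQ-28, larger fall in SR.

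**Step 3: less favourable settings for the artefact.**
- n = 75 per arm, closed form: 87% (ICC 0.3) to 36% (ICC 0.8).
- Alpha 0.05/20 = 0.0025 (critical value 3.02), n = 125, closed form: Φ(4.04 − 3.02) = 84% to Φ(2.09 − 3.02) = 18%. With entry selection, simulated: 90% to 52%. The nominal rate is 0.25%.

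**Step 4: other same-week symptom scales, each with its own error.** The result depends on how the transient variance is built.
- 50–70% stable, 15–30% slowly changing (two-week correlation 0.5–0.7), 15–25% error: about 52–90%.
- 50–80% stable, 10–30% autocorrelated, 10–25% error: 31–81%.
- All transient variance pure error: the nominal 5%.

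**Step 5: possible remedies.**
- Severity × phase × arm: 3.5–7%.
- Screening GHQ-28 as moderator: 4–7% with independent errors, 8–13% with AR(1) 0.3. Stronger autocorrelation was not run.
- Keeping the M1 w1 GHQ-28 and dropping only that SR point: 17–66% under autocorrelated transient variance, so this is not enough.

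**The case against.** The strongest reply is that the plan never says it will test the GHQ-28. The analysis section speaks of RFs, and Table 5 lists the GHQ-28 elsewhere. The broad sentence directly follows one about RFs, and the next paragraph gives the GHQ-28 its role as P. The final list is openly deferred to the observational study. This stands in part: no section names the GHQ-28 as a moderator. But none excludes it, and the broad sentence covers a battery said to include mental health. Deferral does not protect either. A filter that selects predictors of low SR favours a variable that forms SR, if P is measured there as it is here.

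A second reply is that safeguards exist. Supplemental analysis approaches compares associations with the untreated natural course, and the analysis section allows a contrast of the two arms. Both could expose the artefact. However, the first is informal and supplemental, the second is labelled exploratory, and neither changes the within-arm test that comes first.

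A reader might also infer more than the documents support:
- That a false finding is near certain, above nine in ten. This needs an ICC up to about 0.5 without entry selection or about 0.7 with it, at n = 125 and alpha 0.05. The documents fix none of these except the planned total.
- That every baseline symptom scale is equally compromised. The PSS-10, SCL-90-R and STAI are not components of SR, and their inflation rests wholly on an assumed shared transient state.
- That the hypothesised reappraisal and reward-sensitivity moderators of SR fall with it. They are not part of P, and this point does not reach them.

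**Conclusion.** The point holds conditionally. As worded, the sections disagree on whether mental-health measures belong in the pQ1 pool, and the broad wording admits a component of the outcome. If the month 1, week 1 GHQ-28 is tested within an arm as described, it is a false predictor of benefit in roughly 55% to 100% of null trials at 125 per arm and two-sided 0.05. The rate is lower with dropout or a multiplicity-adjusted alpha, but still far above nominal in every setting tried. It rests on assumed stability, autocorrelation and stressor-explained variance, none of which the documents give. For same-week state-symptom scales the rate is about 30–90% if they share an autocorrelated state with the GHQ-28, and 5% if they do not.

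**What to change.** Reconcile Research questions, Online questionnaires and Primary research questions (pQ) so that they define one pool.

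1. State that the baseline-phase GHQ-28 is not a candidate moderator for the within-arm pQ1 tests. This should cover the mean of the three baseline scores as well, which rejected in 93–100% of null runs with entry selection.
2. State that same-week state-symptom scales (PSS-10, SCL-90-R, state part of the STAI) are either not candidates or are reported only with this caveat.
3. If baseline severity is of interest, use the screening GHQ-28, which is already collected, can be linked through the participant code and is not part of baseline SR. Alternatively, report severity × phase × arm.

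The change is one of wording and needs no new data. It has three costs. Same-week severity is lost as a within-arm predictor. The arm contrast cannot show severity moderation common to both interventions, which the plan itself regards as possible for some moderators. The screening score can still exceed 5% modestly when errors are autocorrelated.
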